## Methods/design

This study is a prospective randomized, controlled, double-blind superiority trial which will be conducted as a “specified clinical trial” in accordance with the Clinical Trials Act in Japan. The study will involve 68 patients with hepatobiliary disease and who will undergo hepatectomy at Kansai Medical University Hospital in Japan. The subjects will be allocated randomly into group A (hydrogen gas inhalation group: 34 subjects) and group B (air inhalation group: 34 subjects). Groups A and B will receive 1200 ml/m hydrogen gas and 1200 ml/m air, respectively, via nasal cannula. The respective gas will be administered at least 1 h per time and three times per day, totaling 8 h or less. Air will be used as the placebo comparator to detect the effectiveness of hydrogen inhalation therapy. The air will have no odor, color, or additional effect on postoperative recovery. Moreover, post-hepatectomy patients are typically on room air. Face-to-face adherence reminder sessions will take place at the initial inhalation and at each study visit thereafter. This session includes notification of the total time count of the inhalation period and reinforcement that the study gas may be hydrogen gas or air. No concomitant treatments are prohibited. If a subject will require oxygen, it will be administered via an oxygen mask placed over the nasal cannula. The trial participation period starts after consent attainment and ends at postoperative hospital discharge. The period is expected to be approximately 14–21 days based on our previous experience. The 40-item quality of recovery questionnaire (QoR40) will be used to assess postoperative QOL [6]. The questionnaire will be distributed preoperatively to patients who will independently fill it out themselves. The results will be totaled (perfect score: 200 points) to evaluate postoperative patient satisfaction and recovery level (reference material in the appendix at the end of this paper). The questionnaire survey will be conducted at 10 AM on postoperative day 3.

The results of previous reports infer that hydrogen gas inhalation has wide effects on many aspects, such as on inflammation and liver function, by inhibiting ROS [1–5, 7–10]. The primary endpoint, therefore, is established as the QoR40 on postoperative day 3.

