### Interventions and data collection

From postoperative day 1 to day 7, groups A and B (34 subjects each) will receive 5% hydrogen gas and air, respectively, via nasal cannula for at least 1 h per time and three times per day, totaling 8 h or less (Fig. 1). The study schedule is summarized in Table 1. Upon patient enrollment, the study site staff will make every reasonable effort to follow the participant to ensure that a complete data set is obtained and to avoid associated complexities across the entire study period. All randomized participants who prematurely discontinue study gas inhalation will be considered to be out of the study and will follow the same schedule of events as those participants who continue study gas inhalation, except that the QoR40 and urinary 8-OHdG will not be assessed. All of these participants will be followed until discharge from the hospital as scheduled.

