### Statistical analysis

For the primary analysis, an unpaired *t*-test with common variance (PPS analysis) will be performed to compare the mean of the QoR40 on postoperative day 3 between groups. The subject population to be analyzed will consist of patients who will have consented to trial participation; who will have been administered, according to schedule, at least the minimum dose of their respective gas for at least 2 days; and whose QoR40 on postoperative day 3 will have been measured. The daily minimum dose will be converted to the duration of administration (3-h duration per day) and will be administered in at least 6 h to less than 7 h. In the sensitivity analysis, a *t*-test will be used on the per-protocol population and similarly on a population which includes patients who received insufficient gas. Content with a focus on the non-unique content will be noted in a statistical analysis plan. No compensation for missing data will be made. The statistical significance level will be set at 5% (two-sided) with a confidence interval of 95% (two-sided). No interim analysis will be performed.

For other items, the effects of hydrogen inhalation will be examined by parameters, such as the extent of hepatectomy (segmentectomy or more extensive resection vs subsegmentectomy or less extensive resection) and hepatic ischemia time (30 min or more vs less than 30 min). In addition, comprehensive and exploratory examinations will be performed, including a comparison of patients with high QoR40 scores and patient characteristics.

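### The exposure rule for the primary per-protocol set is internally inconsistent: its hour window has no unit or period, its under-7 h limit has no source, and its two qualifying days are not tied to the time before the endpoint

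*Protocol article*

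**What the plan says.** **Schedule.** Interventions and data collection states: "From postoperative day 1 to day 7, groups A and B (34 subjects each) will receive 5% hydrogen gas and air", given "for at least 1 h per time and three times per day, totaling 8 h or less". Methods/design gives the same session and daily limits.

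**Endpoint time.** Methods/design and Primary endpoint give the same time: "The questionnaire survey will be conducted at 10 AM on postoperative day 3".

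**Primary analysis set.** Statistical analysis admits consenting patients with a day-3 QoR40 "who will have been administered, according to schedule, at least the minimum dose of their respective gas for at least 2 days". The next sentence says that the daily minimum is "converted to the duration of administration (3-h duration per day"), and that it "will be administered in at least 6 h to less than 7 h".

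**Role of the set.** Analysis of efficacy makes the per-protocol population the primary one and adds an intention-to-treat analysis. Statistical analysis also plans a t-test in a wider population that takes in patients who had too little gas.

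**The concern.** The sentence that defines the set gives a minimum. The sentence after it gives a range with an upper end and does not say whether the hours are per day, cumulative or clock time. Different readings select different patients.

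This matters because the rule decides who enters the primary test. The Blinding section says that the principal investigator and the person responsible for statistical analysis know the allocation. A membership rule with several readings, open to interpretation by people who know the allocation, is a weak basis for a confirmatory comparison.

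The second weakness is timing. Exposure that defines a set for a day-3 outcome should precede that outcome. The rule asks for two days without naming them, and dosing continues after the questionnaire.

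**Working it through.** **Inputs, all from the protocol article**

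- Sessions: three a day, at least 1 h each; daily total at most 8 h (Methods/design; Interventions and data collection).
- Dosing days: postoperative days 1 to 7 (Interventions and data collection).
- Endpoint: 10 AM on day 3 (Methods/design; Primary endpoint).
- Per-protocol floor: 3 h per day on at least 2 days (Statistical analysis).
- Hour window: 6 h up to but not including 7 h (Statistical analysis).

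**Step 1. Reproduce the plan's own figure.** The daily minimum is 3 sessions × 1 h = 3 h, as stated. Over two days, 2 × 3 h = 6 h, which is the lower end of the window. So the 6 h is not an error; it is the two-day minimum.

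**Step 2. Look for the upper end.** The schedule's two-day maximum is 2 × 8 h = 16 h, and its one-day maximum is 8 h. Neither gives 7 h, and no other stated figure does.

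**Step 3. Test each reading of the window.**

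| Reading | Schedule allows | Window | Result |
|---|---|---|---|
| Two-day total, used for inclusion | 6 to 16 h | 6 to <7 h, an average of 3.0 to <3.5 h/day | Covers 1 of the 10 permitted hours. A patient at 4 h/day (2 × 4 = 8 h) is on schedule and above the minimum, but outside the window |
| Daily figure | 3 to 8 h | 6 to <7 h | Covers 1 of the 5 permitted hours and contradicts the 3-h daily minimum in the same sentence |
| Clock span over which the 3 h are given | No span stated | 6 to <7 h | No arithmetic conflict, but neither section that sets out the schedule contains such a requirement |

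The shares in the table are shares of permitted hours, not of patients.

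**Step 4. Timing.** Before 10 AM on day 3 there are two complete dosing days, days 1 and 2. Of the seven dosing days, days 4 to 7 fall wholly after the questionnaire and day 3 falls partly after it. The rule's "at least the minimum dose of their respective gas for at least 2 days" does not say which days count. A patient short of gas on day 2 but adequately exposed on days 1 and 4 could therefore be counted as meeting it.

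**The case against.** **The rule is only a floor.** The sentence that defines the population sets no maximum, and the grammatical subject of the 6 to 7 h phrase is the daily minimum dose, not patient eligibility. The wider sensitivity population adds back patients with too little gas; no category exists for too much. This stands in part. A reader might infer that the plan definitely removes well-treated patients, and the documents do not support that: removal follows only if the phrase is applied as an inclusion ceiling. It does not rescue the phrase, because a floor needs no upper end and the text does not say what the upper end is for.

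**It may be a clock window.** This is possible and would remove the conflict in hours. It would then be a timing requirement that appears only in the analysis section.

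**Days 1 and 2 are clearly meant.** Two days and 6 h fit days 1 and 2 exactly, and dosing must follow the schedule, which starts on day 1. A reader might infer that the plan counts gas given after the endpoint. It never says so. What stands is narrower: the rule does not exclude it.

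**Supporting analyses are planned.** The intention-to-treat analysis does not depend on the phrase, which lessens the concern. It is not the primary analysis, however. Interventions and data collection also says that QoR40 is not assessed in participants who stop gas early, and missing data are not filled in.

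**Conclusion.** The point holds as an inconsistency in a stated rule that governs the primary analysis set. It is not a complaint about detail left to an analysis plan. The lower bound of 6 h is sound. The under-7 h limit is unsupported, and the window has no unit or period. Two of its three readings conflict with other text in the protocol, and the third is absent from the schedule. Separately, the two qualifying days are not limited to the time before the outcome.

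The size can be given only in hours: 6 to <7 h against 6 to 16 h permitted over two days, or against 3 to 8 h permitted in one day. How many patients would change status is unknown, because the protocol gives no distribution of inhalation time. A reader might go on to infer a particular loss of power. Any such figure would rest on an assumed share of excluded patients, so none is claimed here. Nor does the article say anything wrong about when set membership is fixed; that is ordinary content for the statistical analysis plan.

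**What to change.** 1. Reconcile Methods/design, Interventions and data collection, and Statistical analysis. State what the 6 to 7 h window measures (hours inhaled or clock time) and over what period, or remove it if it has no purpose.
2. Define the per-protocol set by the minimum exposure only. Any upper limit on inclusion should be no narrower than the reconciled schedule, so that a patient treated within that schedule is classed as compliant.
3. Count only inhalation between the start of gas and the 10 AM day-3 questionnaire, and name the qualifying days.

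This changes how patients are classified for analysis. It proposes no dose or schedule; which schedule text is correct is for the sponsor to settle.

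The cost is one or two sentences. Inhalation time is already recorded per 24 h, which is enough to classify whole days. If the sponsor also wants to count gas on the morning of day 3, session times would be needed, and the article does not say whether they are kept.

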### Analysis of efficacy

The measure of the efficacy of the primary endpoint is the improvement of the QoR40 of the per-protocol population on postoperative day 3. The primary subject population for analysis will be the per-protocol population, but analysis of the intention-to-treat population will also be performed to evaluate the potential for practical application.

### Data monitor

All records related to the clinical trial, including source documents, will be available for trial-related monitoring and inspections by the certified review board and regulatory authorities.

Data monitoring will be performed at the centralized data center at Medical Research Support in Japan.

### Dissemination

The results of this study will be prepared for presentation in a peer-reviewed publication.

### Trial status

The trial is proceeding according to the protocol (version 2.0, 19 November 2020). There will be a total of 68 candidates for study subjects with hepatobiliary disease, for which hepatectomy will be planned at the Kansai Medical University Hospital from protocol approval until 31 December 2022 (Table 2).

**Table 2 Tab2:** Trial data

**Primary registry and trial identifying number**	Japan Registry of Clinical Trial (jRCT): no. 03220332
**Date of registration in primary registry**	Approved on 21 January 2021
**Secondary identifying numbers**	Niigata University Central Review Board of Clinical Research: SP20004
**Source of monetary or material support**	Helix Japan K.K.
**Primary sponsor**	Helix Japan K.K.
**Secondary sponsor(s)**	None
**Contact for public queries**	[name] MD., PhD. [name] of Surgery, Kansai Medical University Email: [contact] Postal address: [name] [contact]
**Contact for scientific queries**	Same as above
**Public title**	Effect of inhalation of hydrogen gas on postoperative recovery
**Scientific title**	Effect of inhalation of hydrogen gas on post-hepatectomy recovery Double-blind randomized controlled trial
**Countries of recruitment**	Japan
**Health condition or problem studied**	Hepatobiliary diseases
**Intervention(s)**	Inhalation of hydrogen gas
**Key inclusion and exclusion criteria**	Inclusion criteria: 1. 20 years old and older (regardless of gender) 2. Patient has undergone hepatic resection for hepatobiliary cancer (regardless of the operative procedure, range of hepatectomy, and primary disease) 3. Patient who accepts entry to this study with free will after sufficient explanation Exclusion criteria: 1. Severe liver dysfunction or severe renal dysfunction 2. Uncontrollable diabetes mellitus 3. Pregnancy or possibility of being pregnant 4. Lactating patient 5. Patient who received another test agent or investigational agent within three months prior to agreement for this study 6. Patient who required combined other organ resection (stomach, colon, lung, and so on) 7. Patient who required biliary tract reconstruction 8. Patient who required emergency surgery (HCC rupture) 9. Patient who is considered as inadequate by the principal investigator of this study
**Study type**	Interventional, randomized controlled trial/double blind/placebo or control/parallel assignment/treatment purpose
**Date of first enrollment**	9 March 2021
**Sample size**	68
**Recruitment status**	Recruiting
**Primary outcome**	QoR40 of postoperative day 3
**Key secondary outcomes**	1. QoR40 except postoperative day 3 2. Postoperative complications (Clavien-Dindo score) 3. Wound pain (Numerical Rating Scale) 4. Dietary intake 5. The number of steps taken 6. Inflammatory response (WBC, CRP, neutrophils, lymphocyte) 7. Liver functions (total bilirubin, AST, ALT, ALP, albumin, thrombocyte, PT, ICG) 8. Reactive oxygen value (urinary 8-OHdG) 9. Adverse event 10. Time of inhalation of hydrogen gas
**Ethics review**	Approved Approved number: SP20004 Date of approval: 19 January 2021 Ethics committee: Niigata University Central Review Board of Clinical Research Address: [name]
**Completion date**	31 December 2023
**Summary results**	No results for now
**IPD sharing statement**	Plan to share IPD: no

*QoR40* the 40-item quality of recovery questionnaire, *CRP* C-reactive protein, *AST* Aspartate transaminase, *ALT* Alanine transaminase, *ALP* Alkaline phosphatase, *PT* Prothrombin time, *ICG* Indocyanine green, *8-OHdG* 8-hydroxy-2’-deoxyguanosine, *IPD* individual clinical trial participant-level data

### Study timeline

Total study period: Japan Registry of Clinical Trial (jRCT) publication day—2023 December 31

Enrollment period: jRCT publication day—2022 December 31

## Data Availability

For protection of privacy of participants, the datasets analyzed during the current study have not been made publicly available, but they can be obtained from the corresponding authors if there are reasonable requirements.
